**Fig. 2 Fig2:**
[figure not shown]
Flow diagram of ‘Learn to Dare!’ study

Parents (and children, when they are 12 or older) send a signed informed consent form to our university, after which they receive an automatically generated e-mail with their account information. With this account, the children have access to the screening questionnaire on the platform. The authors that will be responsible for data analyses do not have access to the accounts and are completely blinded from participants’ information.

We use the Youth Anxiety Measure for DSM-5 (YAM-5, [54, 55]) as a screening tool and to measure the development of anxiety over time. When completing the YAM-5, children also fill in their demographic features. Children who score in the highest quartile are labelled as high-anxious. We use different cut-offs for boys and girls in order to increase the chance of a proportional influx of boys and girls. All other children are excluded and receive a message that they are not severely anxious, and that the program is not intended to suit their level of anxiety. These children receive links to general anxiety websites for children.

Consecutively, the high-anxious children are invited by e-mail to book a date for a diagnostic interview. The diagnostic interview Structured Clinical Interview for DSM-5 Disorders for Children (SCID, [56]) is performed by telephone with a trained interviewer. If the SCID shows that a child suffers from a severe anxiety disorder other than specific phobias, the child is excluded from the study. In this case, the first author does get access to the accounts of the participants (unblinding) as the parents are contacted by phone. Parents are advised by the first author to seek help for their child at a local mental health care institution.

The study concerns a randomized controlled trial (RCT). Within the ‘Learn to Dare!’ platform, the included high-anxious children are automatically randomized to the intervention group or to the waitlist control group. Children in the waitlist control group can participate in the intervention too after the last assessment point. We apply block randomization with child’s age and sex as strata. If children are randomized to the intervention group, they are assigned personal trainer who helps them during the training. The intervention and assessments are aimed at the children only.

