Children in both groups perform the same assessments, which are all online within the ‘Learn to Dare!’ platform. Assessment points are aligned with the mediators, which means they take place before and after exposure and cognitive restructuring is offered to the children. At every assessment point child anxiety, avoidance behavior and dysfunctional cognitions are measured. The assessments are embedded in the intervention program, and take place after session 1 (after psycho-education and before the child’s expectancies are made explicit), after session 3 (before the start of actual exposures), after session 5 (before the start of cognitive restructuring), and at the end of the training. Control children receive automatically generated e-mails to notify them they have to complete an assessment. A follow-up assessment takes place 12 weeks after the last session. Both the intervention children and control children receive an automatically generated e-mail to notify they have to complete this assessment. At the follow-up assessment, the children take part in the diagnostic interview again. If children do not complete an assessment or intervention session, they will receive automatically generated reminders by e-mail twice. A research assistant also monitors the progress of the children and of the interviewers and trainers.

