**Fig. 3 Fig3:**
[figure not shown]
‘Learn to Dare’ intervention. *Note.* Sessions in consecutive order: 1. Getting to know each other, 2. Catching anxieties, 3. Making tracking plans, 4. Defy, 5. Dare, 6. Tracing thoughts, 7. Thought helpers, 8. Saying goodbye; Source of images: Simon, E., & Bögels, S. M. (2013). *Leer te durven! Werkboek*. Houten, Lannoo Campus. The first author has obtained written permission to use and adapt the figures for research purposes

At the start of the intervention, the trainer has to select two domains of anxiety that are targeted in the Learn to Dare program. These anxiety domains are selected by the following method: First, the trainer checks the SCID-Junior data to see if a DSM-5 classification exists for this child. If one or two classifications apply, these are selected to be targeted in the intervention (e.g. fear of heights; social anxiety). In case of more than two classifications, specific phobias are given priority over other anxiety disorders. In case of no DSM-5 classifications, the trainer checks the YAM-5 data and picks two types of anxiety, prioritizing specific phobias. The selected anxiety domains are entered in the system and will serve as targets in the intervention. The order in which the domains are targeted is randomized within the system, which means not the trainer but the system decides which anxiety domain will be targeted with exposure and which domain with cognitive restructuring. This minimizes chances of (unwanted) manipulation of the trainer (e.g. always target specific phobias with exposure and always target generalized anxiety with cognitive restructuring).

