To test the primary research question, we will use regression model with the outcome Anxiety Level (AL) as dependent variable and condition (LTD vs WL) as predictor. Sex and Age will be added as extra predictors, plus interactions between predictors to see if the effects differ per sex and age category (LC). Model: AL = b0 + b1*Group + b2*Sex + b3*LC + b4*Group*Sex + b5*Condition*LC. To test the moderation and mediation models, we will use multilevel analysis [64]. The five assessments (T1,T2,T3,T4,T5) will be the lowest level, the children the second level. This model can be considered a moderated mediation model (Hayes, 2013). The mediation analysis will consist of 2 steps. 1st: Dysfunctional Cognitions (DC) and Avoidance Behavior (AB) will be dependent variables, in separate analyses. 2nd: Anxiety level (AL) will be the dependent variable. Time will be added and modelled as T = 0,1,2,3,4, to tested the linear increase of Anxiety Level (AL) during the intervention. We will use a random intercept model, because we expect individual differences to exist in the levels of DC, AB, AL. Step 1. DC = b0 + b1*Group + b2*Time VG = b0 + b1*Group + b2*Time. Step2. AL = b0 + b1*Group + b2*VG + b3*DC. To test the third hypothesis (moderation by cognitive level), we will perform a multilevel analysis as above. 1st: Dysfunctional Cognitions (DC) and Avoidance Behavior (AB) will be dependent variables, in separate analyses. Cognitive Level (CL) will be added as predictor in a hierarchical linear multilevel model, including the interaction with condition to test for the moderating effect of CL on the relation between condition and mediators. Time will be added and modelled as T = 0,1,2,3,4, to tested the linear increase of DC and AB during the intervention. We will use a random intercept model, because we expect individual differences to exist in the levels of DC and AB. DC = b0 + b1*Group + b2*CL + b3*Group*CL + b4*Time VG = b0 + b1*Group + b2*CL + b3*Group*CL + b4*Time. The variable Cognitive Level (CL) will be centered at zero. For the follow-ups, when interaction effects appear to be significant, simple slopes plots will be made to illustrate the interaction effect. The 95% confidence interval of the parameter estimates of the multilevel and logistic regression analyses will be used to assess the statistical and practical significance of the estimates. The standardized parameter estimates will be used as estimated effect sizes. For all interval variables univariate outlier detection will be applied by using the Inter Quartile Range (IQR): scores outside 1.5*IQR will be examined, in order to see whether these are genuine scores, and cannot be attributed to coding or other errors. If they are genuine the scores remain in the analysis, otherwise they are removed from the analysis. Since we will use multilevel analyses drop-outs can be kept in the analysis. Subjects with at least one wave (time point) with complete data will be used in the analysis. No imputation strategy will be applied. We will explore the time factor in more detail. Other coding schemes than a simple linear coding will be tested to see whether effect gradually weaken in time or take effect after a certain period. Furthermore, we will explore whether the proposed model has predictive value for the binary outcome (anxiety diagnosis).

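### The exploratory analysis of anxiety diagnosis points to a model whose printed equations omit the baseline SCID diagnosis, a free covariate that would sharpen the result and make it easier to read

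*Protocol article*

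**What the plan says.** The Procedure section describes a diagnostic interview before randomisation: "the high-anxious children are invited by e-mail to book a date for a diagnostic interview". Children with a severe disorder other than specific phobia are then excluded, and those who remain are randomised, in blocks stratified by age and sex. The interview is repeated 12 weeks after the last session: "At the follow-up assessment, the children take part in the diagnostic interview again".

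The Participants section admits children with high anxiety, specific phobias or other mild anxiety disorders. The Intervention section shows that some randomised children have no disorder at entry: "In case of no DSM-5 classifications, the trainer checks the YAM-5 data". It also has rules for one or two classifications and for more than two.

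Under Analyses, the diagnosis outcome gets one sentence: "we will explore whether the proposed model has predictive value for the binary outcome (anxiety diagnosis". The equations printed there are:
- primary question: "AL = b0 + b1*Group + b2*Sex + b3*LC + b4*Group*Sex + b5*Condition*LC"
- mediation, step 2: "AL = b0 + b1*Group + b2*VG + b3*DC"
- moderation: "DC = b0 + b1*Group + b2*CL + b3*Group*CL + b4*Time", with a matching equation for avoidance.

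Logistic regression is mentioned once, in "The 95% confidence interval of the parameter estimates of the multilevel and logistic regression analyses", without a list of its terms.

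**The concern.** The SCID is the only interview-based outcome; the other outcome and mediator measures are child self-report. Each randomised child should have a SCID from before randomisation, and baseline diagnosis is likely to be a strong predictor of diagnosis at follow-up. If the binary analysis takes over the printed terms, that information goes unused.

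Two things are at stake. The first is interpretation: a difference in follow-up prevalence could come from more remission among children who entered with a diagnosis, fewer new diagnoses among those who did not, or both. The second is precision: leaving out a strong prognostic covariate from a logistic model costs power for the group effect. Stratifying on age and sex does not guard against chance imbalance in baseline diagnosis either.

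**Working it through.** **The plan's own figure.** The Participants section gives 240 children (120 per arm) for 80% power of the direct and indirect pathways, from a simulation whose numerical inputs are not printed, so it cannot be reproduced. Taking a medium direct effect as d = 0.5 (an assumption), two-sided 5% and 80% power, the direct effect alone needs 63 per arm, or 63 / 0.9^4 = 97 after four losses of 10%. No power target is stated for diagnosis, so nothing below changes the 240.

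**Is baseline diagnosis in the model?** The terms in the three equations quoted above are group, sex, LC (age category), VG (avoidance), DC (dysfunctional cognitions), CL (cognitive level), time and interactions. Baseline diagnosis is not among them. The five assessments coded T = 0 to 4 are after session 1, after session 3, after session 5, at the end of training, and at follow-up. The screening SCID precedes all five.

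**Inputs for the size.** From the article: 120 per arm and 10% drop-out between measurements, so 120 × 0.9^4 = 78.7, about 79 per arm after four intervals. Not in the article, and therefore assumed: the share with a baseline diagnosis, persistence and onset on the waitlist, and the conditional odds ratio. The test is two-sided at 5%.

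**One case by hand.** Half the children have a baseline diagnosis, waitlist persistence is 0.70, onset 0.15 and the conditional odds ratio 0.45.
- Waitlist prevalence: 0.5 × 0.70 + 0.5 × 0.15 = 0.425.
- Intervention persistence: odds 0.70/0.30 × 0.45 = 1.05, so 1.05/2.05 = 0.512.
- Intervention onset: odds 0.15/0.85 × 0.45 = 0.079, so 0.079/1.079 = 0.074.
- Intervention prevalence: 0.5 × 0.512 + 0.5 × 0.074 = 0.293.
- Marginal odds ratio: (0.293/0.707) / (0.425/0.575) = 0.56.

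**Simulated power.** Logistic regression of follow-up diagnosis on group, without and with baseline diagnosis, odds ratio 0.45, 2,000 trials per setting (standard error of one power estimate at most √(0.25/2000) = 1.1 points). Selected settings:

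| Baseline diagnosis | Persistence / onset | 120 per arm, without → with | 79 per arm, without → with | Marginal OR |
|---|---|---|---|---|
| 30% | 80% / 10% | 0.304 → 0.502 | 0.197 → 0.325 | 0.65 |
| 50% | 60% / 30% | 0.777 → 0.803 | 0.583 → 0.623 | 0.48 |
| 50% | 70% / 15% | 0.577 → 0.707 | 0.393 → 0.517 | 0.56 |
| 50% | 80% / 10% | 0.392 → 0.605 | 0.281 → 0.445 | 0.64 |
| 90% | 60% / 30% | 0.836 → 0.855 | 0.650 → 0.675 | 0.46 |
| 90% | 80% / 10% | 0.653 → 0.742 | 0.504 → 0.571 | 0.52 |

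Over the full grid (30%, 50%, 70% and 90% with a baseline diagnosis), the gain is about 2 to 21 points at 120 per arm and about 3 to 16 at 79.

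**A second set of assumptions.** With odds ratio 0.40, 40 to 60% with a baseline diagnosis, persistence 60 to 80% and onset 10 to 20%, the gain per setting is about 4 to 24 points. Outside those ranges it shrinks: 2 to 4 points at 60% persistence with 30% onset, and 1 to 8 points when 90% have a baseline diagnosis. In a setting with no effect, the adjusted test rejected in 5.5% of trials, close to nominal.

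**The case against.** The strongest reply is that the article prints no logistic equation for this outcome and points to a preregistered plan that is not shown. A reader might infer that the plan definitely leaves out the baseline SCID; the documents do not support that. What they do show is that the outcome is referred to a model whose equations are written out term by term without it. Adding it is an improvement on that stated model, not a request for missing detail.

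A repeated-measures version of the model might carry the baseline SCID as an outcome row. The printed time coding does not support this, because its first assessment comes after session 1 and the screening interview has no place in it.

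A reader might also infer from the smaller unadjusted odds ratio (0.45 becoming 0.46 to 0.65 over the grid) that the group comparison is biased. It is not. Under randomisation, the difference in follow-up prevalence is estimated without bias. The marginal and conditional odds ratios are different quantities, and the gap between them is non-collapsibility.

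Three further points stand. The sentence speaks of predictive value, whereas the power figures concern only the group term. The rates are all assumed, and the gain is small in some settings. A yes/no covariate is also coarse: a child who loses one disorder and gains another counts as persistent.

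**Conclusion.** The point holds as a minor one. The printed equations to which the diagnosis outcome is referred leave out a baseline value already collected, and follow-up diagnosis combines persistence with onset. The cost is in precision and interpretation, not validity. Its size cannot be taken from the article: under the assumed rates it is roughly 1 to 24 points of power for the group effect. The high end needs baseline diagnosis to be a strong predictor; the low end applies when it predicts weakly or nearly all children have a diagnosis. It would be tempting to conclude that the trial is underpowered, but the analysis is exploratory with no power target, so the 240 and the 80% stand.

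**What to change.** State that the exploratory logistic model for follow-up SCID diagnosis includes baseline SCID anxiety diagnosis (yes/no) as a covariate. Alongside it, describe by arm the proportion in remission among children with a baseline diagnosis and the proportion with onset among those without. Say how any-diagnosis coding treats a child whose disorder changes. If the preregistered plan already does this, one sentence in the article is enough.

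The cost is one covariate and a small descriptive table, with no new data or visits and no change to the sample size. Fixing this before the data are analysed also removes a later choice between adjusted and unadjusted results. The analysis remains exploratory.

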
## Discussion

Offering easy accessible interventions and providing insight into the working mechanisms of Cognitive Behavioral Therapy will contribute to optimizing Cognitive Behavioral Therapy for anxious youth.

## Data Availability

A detailed study design and analysis plan were preregistered at https://osf.io/g2avh, supporting data can be accessed via this register in the Open Science Framework.

## Abbreviations

AB: Avoidance Behavior
AL: Anxiety level
CATS-N/P: Children’s Automatic Thoughts Scale – Negative/Positive
CBT: Cognitive Behavioral Therapy
CL: Cognitive Level
CMS: Content Management System
CR: Conditional Reaction
CS: Conditional Stimulus
DC: Dysfunctional Cognition
DSM: Diagnostic and Statistical Manual of Mental Disorders
IQR: Inter Quartile Range
LAMP: Linux Apache MysqlPHP
LTD: Learn to Dare
RCT: Randomized Controlled Trial
SCID: Structured Clinical Interview for DSM-5 Disorders for children
US: Unconditional Stimulus
WL: Waitlist
YAM-5: Youth Anxiety Measure for DSM-5
